#### Nonexperimental (Observational) Design

Two different comparisons will be established. In the first comparison (addressing objective 2 question 6) an as-treated analysis of the trial data will be conducted where individual students assigned to the Tobacco-free Duo intervention and signing a child-adult contract will be contrasted to students receiving other Tobacco-free Duo components but not signing the contract. In the second comparison (addressing objective 3 question 7), all students attending schools in grades 7 to 9 in both experimental groups will be contrasted to students in a convenience sample of schools in the same broad catchment areas where the experiment takes place (an external reference group). Schools in this external reference group will be those willing to participate in the survey data collection but not in the experimental study. Therefore, they will represent the subset of schools in the target areas that will probably not be willing to adopt the program once released for dissemination. In Table 2, a summary is presented of the relevant comparisons established with an observational design.

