#### Experimental Design

A parallel cluster randomized controlled experiment will be conducted with schools as units of randomization and individual students as unit of analysis. A superiority approach will be employed for hypothesis testing (ie, the null hypothesis to be rejected will be that the Tobacco-free Duo comprehensive intervention is either inferior or equivalent to the education-only component). Through this design, questions 1 to 5 will be addressed (Tables 1 and 2). The trial was registered (ISRCTN 52858080) on January 4, 2019 (ie, after enrollment of the first participant but prior to baseline assessments being completed).

**Table 1 table1:** Evaluation questions.

Objective–question		Formal question definition	

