**Objective 3**			
	Question 7		Is the total prevalence of never smokers among students in the grades 7 to 9 declining more slowly over 3 years in Tobacco-free Duo schools compared to education-only schools or schools delivering their usual antismoking programs (external reference group schools)?

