	**Decline in school prevalence of never smokers**		
		Population	Students registered in the grades 7-9 of the schools participating in the experimental study and in the schools serving as external reference during three consecutive years
		Intervention 1	Tobacco-free Duo 6 components (as treated)
		Intervention 2	Educational component of Tobacco-free Duo only (as treated)
		Comparator	Usual education or health promotion
		Outcome	Average point prevalence of never smoking in spring term of each school year

^a^PICO: population, intervention, comparator, outcome.

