#### Data Analysis

Data from the trial will be analyzed primarily according to an intention-to-treat approach, preserving the random assignment [28]. Missing outcome information because of attrition at follow-up will be addressed by means of sensitivity analyses including last observation carried forward; best- and worst-case scenario, assuming missing answers as representing either the best or the worst outcome; and multiple imputation if a missing at random assumption for the missing data will not be dismissed [29].

Secondary analyses will be conducted per protocol, thus including only students in schools that adhered to at least 80% of the whole assigned intervention. Furthermore, an as-treated analysis will be conducted, comparing the outcome among students exposed to different components and intensities of the intervention, in particular the adoption of the core component *child-adult agreement* (research question 6). These approaches disregard randomization, therefore they are prone to producing biased estimates of the effect unless adjusted for most of the potential confounders [30]. However, they may be useful in order to assess the consistency between an expected effect and the intervention’s theoretical rationale [30] and in order to gain insights on the reasons for not detecting the estimated effect [31].

Finally, we will be able to compare the prevalence trends across 3 school years as well as the final prevalence at the end of follow-up between schools participating in the experimental study and schools in the external reference group, carrying on usual health education. This will enable us to estimate the potential impact of the intervention when released.

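### Question 7 names education-only schools as a comparator, but the passages that specify its analysis treat it as observational and do not specify the randomised Duo v education-only contrast on whole-school never-smoking

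*Protocol article*

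**What the plan says.** Table 1 (Objective 3, Question 7) asks whether the prevalence of never smokers in grades 7 to 9 is "declining more slowly over 3 years in Tobacco-free Duo schools compared to education-only schools or schools delivering their usual antismoking programs". Two comparators are named: education-only schools, which are the other randomised arm, and the external reference schools.

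Three places specify how the question will be analysed:

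- **Nonexperimental (Observational) Design** assigns Question 7 to the second observational comparison, in which "all students attending schools in grades 7 to 9 in both experimental groups will be contrasted to students in a convenience sample of schools".
- **Table 2**, in the nonexperimental block on the decline in school prevalence, lists Duo as Intervention 1 and "Educational component of Tobacco-free Duo only (as treated") as Intervention 2. Both carry the as-treated label. The only comparator is "Usual education or health promotion".
- **Data Analysis** compares prevalence trends and final prevalence "between schools participating in the experimental study and schools in the external reference group".

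The reference schools are a convenience sample. Under Invitation and Selection of Schools, they are schools that were not willing to be randomised but agreed to be surveyed.

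**The concern.** Experimental Design and Randomization make the school the unit of allocation. Table 3 plans anonymous surveys of all grade 7 to 9 students in Duo, education-only and reference schools at the end of school years 1, 2 and 3. The first half of Question 7 is therefore a randomised comparison at the level at which randomisation took place, on data that will be collected anyway. The analysis text leaves this comparison out and keeps only the non-randomised one.

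The contrast that remains mixes up to three things: what the Duo components add to the lessons, what the lessons do by themselves, and how schools that accept randomisation differ from schools that decline it. The article itself says that the reference schools are probably those that would not adopt the program. If only this contrast is reported, a difference cannot be attributed to Duo, and the absence of a difference cannot be read as showing that Duo adds nothing to the lessons.

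**Working it through.** **Question against analysis.** The plan states no figure for Question 7, so the check is of the text.

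| Place | Comparator for Question 7 | How groups are described |
|---|---|---|
| Table 1, Question 7 | Education-only schools, or reference schools | Duo schools, education-only schools |
| Nonexperimental Design | Reference schools | Both experimental groups |
| Table 2 | Usual education | Two interventions, as treated |
| Data Analysis | Reference schools | Schools in the experimental study |
| Discussion | Reference schools | Schools randomised to minimal or comprehensive intervention |

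Education-only is a comparator in the first row and in none of the others. The as-treated label in Table 2 also disagrees with the Discussion, which describes the same groups by randomisation.

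**What a trial v reference contrast estimates.** Let d be Duo minus education-only, and e be education-only minus reference (lessons plus self-selection).

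- Duo v reference estimates d + e.
- Education-only v reference estimates e.
- If the arms were combined, with an assumed 22 and 21 schools out of the 43 recruited, the contrast would estimate e + (22/43)d, about e + 0.51d.
- Only Duo v education-only estimates d directly and by randomisation.

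**Conditional illustration.** This applies only to an analysis of prevalence at the end of follow-up.

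- *Inputs from the article:* never-smoking 0.70 and intraclass correlation 0.02 (sample-size section); 43 trial and 16 reference schools (Results).
- *Assumed:* a 22/21 split, 225 surveyed students per school (range 150 to 300), and a two-sided 5% test.
- *Variance of a school prevalence:* 0.70 × 0.30 × (1 + 224 × 0.02)/225 = 0.21 × 5.48/225 = 0.00511.
- *Standard errors:* Duo v education-only, √(0.00511 × (1/22 + 1/21)) = 0.0218. All trial schools v reference, √(0.00511 × (1/43 + 1/16)) = 0.0209. Duo alone v reference, √(0.00511 × (1/22 + 1/16)) = 0.0235.

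Results from the noncentral t distribution, with 41, 57 and 36 degrees of freedom respectively:

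| Scenario | Contrast | Probability of significance (range) |
|---|---|---|
| d = 0; e = 3, 5 or 7 points | Combined arms v reference | 29%, 65%, 91% (27–30%, 61–67%, 88–92%) |
| d = 0, any e | Duo v education-only | 5% |
| e = 0; d = 7 points (0.70 to 0.77) | Combined arms v reference | about 39% (36–41%), estimating 7 × 22/43 = 3.6 points |
| e = 0; d = 7 points | Duo alone v reference | about 83% (79–84%) |
| e = 0; d = 7 points | Duo v education-only | about 88% (85–89%) |

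The combined-arm rows hold only if the arms are in fact combined. The 0.70 is the article's ninth-grade planning value for the primary outcome, not a whole-school figure.

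**The case against.** The strongest reply is that the contrast is only unstated. Table 1 is the formal definition of the question and includes education-only schools. The Abstract lists a whole-school repeated cross-sectional approach among the methods for the trial data and introduces the observational study separately. Data Analysis opens with a general commitment to intention to treat. This stands as a reason to write *not specified* rather than *abandoned*. It does not remove the problem: neither passage names a whole-school Duo v education-only contrast, and the passages that do deal with Question 7 place it elsewhere.

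Four stronger readings are tempting and are not supported:

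- **That the arms will be pooled.** The wording in the design section and Data Analysis allows it, but Table 2 lists two separate interventions against one comparator. If the arms stay separate, the diluted effect and the 39% power disappear, and Duo v reference has about 83%.
- **That a 29% to 91% false-positive rate follows.** Question 7 and Data Analysis also compare trends, and a stable difference in level between willing and unwilling schools would cancel there. The Discussion also mentions comparison across school-level characteristics. Part of e may be a real effect of the lessons, which are themselves a Duo component.
- **That Question 7 was deliberately excluded from the trial because** "Through this design, questions 1 to 5 will be addressed". The numbering is unreliable: contract signing is Question 5 in Table 1 but question 6 in the Nonexperimental Design and Data Analysis sections.
- **That as-treated grouping favours Duo.** This is plausible, but no rule for reclassifying schools is given for Question 7, so the direction is not shown.

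The reference comparison also has a legitimate stated purpose, projecting impact on release, and its selection limits are disclosed. That is a reason to keep it. It does not answer the education-only half of Question 7.

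**Conclusion.** The inconsistency is real and worth correcting. Table 1 asks for Duo v education-only at whole-school level, and the passages that specify the analysis name only self-selected reference schools as comparator. As written, Objective 3 would have only an estimate confounded by willingness to be randomised, although the design supplies a randomised one.

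The reach is limited. Objective 3 is worded as exploratory in the Introduction. What Duo adds to the lessons is tested by Questions 1 to 4 in the randomised cohort, and the primary analysis is unaffected. The conclusion rests on the text alone. The error rates and the diluted effect are conditional on combined arms, end-of-follow-up prevalence and an assumed number of students per school, and should not be quoted as properties of the plan.

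**What to change.** In Table 2, the Nonexperimental Design section and Data Analysis, split Question 7 in two:

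1. **Lead analysis (experimental).** Duo v education-only schools by assigned arm, intention to treat, allowing for clustering by school, over the three annual whole-school surveys. Education-only is entered as comparator in Table 2.
2. **Supportive analysis (observational).** Each trial arm compared separately with the reference schools, with a statement that the arms are not combined.

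Keep as-treated grouping for Question 7 only as a sensitivity analysis. Update the list of questions in Experimental Design to match, and correct the Question 5 / question 6 numbering at the same time.

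The cost is the rewording and one extra analysis. No new schools, surveys or data are needed. The claim drawn from the reference-school contrast becomes slightly weaker.

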### Intervention Implementation and Fidelity (Objective 5)

As a complement to the evaluation of effectiveness, we plan to monitor and describe the implementation of the Tobacco-free Duo intervention, in particular the average proportion of schools and classes delivering the intervention components as intended; the observed versus expected frequency of delivery of each of the 6 components and their range; and the characteristics of the schools not conducting or completing the program as intended and alleged reasons for this failure.

### Adolescents’ Experiences and Reported Side Effects of the Intervention (Objective 4)

We plan to identify negative outcomes of the intervention, particularly those connected with the administration of the core component agreement between an adult and a child. We will use the conceptual framework proposed by Lorenc and collaborators [27] to identify adverse effects in 2 domains: psychological side effects and equity side effects. Specifically, we will use adolescent questionnaire data to explore unequal distribution of application of the core components across socioeconomic status and composition of the index families (equity aspect). Reasons for not signing a contract or changing contract partner, satisfaction with the partnership, and perception of the partner’s support will also be explored (psychological aspects), both through questionnaire data and through in-depth interviews with adolescents. To this end, a convenience sample of both contract holders and nonholders will be enrolled.

### Study Procedures

#### Invitation and Selection of Schools

All schools located in 11 regions of central and south Sweden encompassing the higher block grades (7 to 9) will be invited to participate in the study through a letter addressed to the school’s headmaster at the end of the school year preceding the conduction of the intervention. We estimate this underlying source sample as about 600 schools. Schools will be eligible if they have at least 2 classes in the target grades and if they did not or do not plan to adopt the Tobacco-free Duo program until the evaluation is completed. The eligibility criteria will be assessed among respondents willing to participate through a questionnaire on school organization and characteristics sent concurrently with the invitation.

The final selection will rest on a formal agreement issued by the school headmaster to be randomly assigned to the intervention or comparator condition, to engage the school personnel in the training for and in the delivery of the intervention, and to facilitate the data collection. We estimate that at least 40 schools will be recruited into the experimental study.

Schools not willing to be randomized will be asked if they are willing to participate as part of the external reference group (ie, to deliver and report on the usual antismoking program if any and to collect data from students in repeated anonymous cross-sectional surveys).

#### Randomization

After recruitment, the consenting schools will be simultaneously randomly assigned to either the full program (Tobacco-free Duo) or to the education-only component of the same program. The random assignment will be performed by a statistician based at the steering group through a computer-generated series of random numbers, paired to each school, after stratification into publicly and privately run schools.

The results of the randomization will not be disclosed to the participating schools until the beginning of the school year during which the intervention will be delivered. Because of the nature of the interventions, blinding of participants will not be possible.

#### Identification and Enrollment in the Trial of Individual Students

Based on the school rosters, all students attending the seventh grade in the beginning of the school year will potentially be eligible for participation in the study. Besides the information delivered in class and school (see components 2 and 3), an individual invitation letter is sent to students’ home addresses, and individual parental consent will be sought with an opt-in procedure. In the invitation, it will be underlined that it will be possible to withdraw the assumed consent any time, both from the parents’ side and from the student’s side. Also, it will be clarified that the consent to participation concerns the baseline and follow-up collection of information to be entered in a register with personal identifiers but not the receipt of the intervention. The latter is decided at the school level, therefore not submitted to any individual consent, similar to any school-based activity.

Based on previous experience, we foresee that we will be able to enroll approximately 85% of the eligible students in the seventh grade. All recruitment procedures will be conducted by an executive team composed of research officers under the guidance of the principal investigators.

#### Training of School Personnel

School staff involved in the study are offered an annual meeting with education, training, and networking in their respective experimental group (Tobacco-free Duo school or education-only school). The content of the meeting is diversified according to the assigned intervention, with a common part regarding instructions for data collection and the educational intervention component. The aim is to gradually increase the personnel’s knowledge, to give an opportunity for exchange of experiences during the project period, and assure quality of data collection over time. The meetings are scheduled to be held annually before the fall term start, separately for education-only and Tobacco-free Duo schools.

#### Delivery of the Interventions

The school leadership at each participating school nominates a contact person and constitutes an operative team responsible for the implementation of the assigned intervention. The contact person will be responsible for contacts with the research group and for convening the school’s operative team. This includes the contact person, one or more persons from the student health care team, and one or more teachers in grades 7-9. Together they are responsible for the implementation of the assigned intervention components.

### Data Collection and Management

At both baseline and follow-up, information on outcome and predictor variables will be collected at 2 levels.

School-level information will encompass compositional and organization measures such as number of registered students and staff, staff average qualification, proportion of students with parents with lower than high school education, proportion of students with parents born outside Sweden, public or private management, and prior and current health promotion initiatives or preventive programs. Structured checklists and questionnaire forms will be developed.

In schools participating in the experimental part of the study, information will be continuously collected about the actual implementation of the intervention components and staff effort dedicated to them. To this end, a structured web-based form will be used.

Individual-level information will be gathered from individual students in Tobacco-free Duo schools, education-only schools, and reference group schools; from parents of students in Tobacco-free Duo and education-only schools; and adults in Tobacco-free Duo schools signing the contract with individual students, when not coinciding with one parent. All information will be collected with self-completed structured questionnaires with different content and administered with different procedures as shown in Table 3. All questionnaires will be based on sets of questions that have been previously used in Swedish surveys or longitudinal studies of tobacco use in youths. Individual participants in the experimental study will be traced through school records, even in cases of change of school or residence address. In fact, during compulsory education, changes of schools are registered at both ends of the transition (former and new school). Those absent during data collection days will be reached at their latest registered residence addresses.

**Table 3 table3:** Data collection instruments, information, and procedures.

Population	Instrument and main domains	Administration	Identifier	Time-points
Participating students in schools randomized to Tobacco-free Duo or education only	Paper questionnaire, with information on: Cigarette and snus use (any, current, frequency, quitting) Tobacco use among friends and family members Received education, knowledge and attitudes toward tobacco Recent and current use of alcohol Ever use of illicit drugs General health, physical activity, and sedentary time Perceptions about the contract (if appropriate)	Self-administered in the classroom	Unique study code matched to identity information	Baseline: fall term of school year 1- grade 7 Follow-up 1: end of school year, grade 7 Follow-up 2: end of school year 2, grade 8 Follow-up 3: end of school year 3. grade 9
Guardians of the participating students above	Paper questionnaire, with information on: Sociodemographics Relation with the index child and perception of risks with tobacco use Own tobacco and alcohol use	Self-administered at home	Same code as the index child above	Same time points as above
Adults in Tobacco-free Duo pairs	Paper questionnaire, with information on: Own use of cigarette and snus Perception of own role in the intervention	Self-administered at home	Same code as the index child above	Anytime a contract is signed
All students registered in Tobacco-free Duo schools, education-only schools and reference group schools in grades 7-9	Paper questionnaire, with information on: Ever, regular and recent use of cigarette and snus	Self-administered in the classroom	No identifier (anonymous survey)	Cross-sectional surveys at the end of school year 1, 2 and 3

Figure 1 displays a scheme of the participants’ enrollment and assessments time-points for the experimental part of the study.

Individual data from questionnaires will be optically scanned, and the corresponding electronic files will be stored in a password-protected section of the server at the Department of Global Public Health, Karolinska Institutet. In order to preserve strict confidentiality, this data will be stored without personal identifiers, substituted by a study code unique to each participant. Personal identifiers will be kept in a separate section of the same server, only accessible to 2 members of the study team, responsible for data linkage and follow-up procedures, respectively. Ten years after the study start the personal identifiers will be removed and all information will be kept identified only through the study code.

